# Effect of a Personalized Mobile Health Intervention Using Artificial Intelligence (the WARIFA App) Versus a Nonpersonalized Intervention on User-Defined Objectives, Healthy Lifestyles, and Management of Type 1 Diabetes (T1D): Protocol for a Randomized Controlled Trial

**DOI:** 10.2196/84510

**Published:** 2026-05-22

**Keywords:** noncommunicable diseases, type 1 diabetes, mHealth app, mobile health, artificial intelligence, behavior change, lifestyle, user-centered

## Abstract

**Background:**

Noncommunicable diseases are the leading cause of death worldwide. Cardiovascular and respiratory diseases, cancer, and type 2 diabetes share common risk factors that can be addressed: physical activity, a healthy diet, and avoiding smoking and alcohol. The Watching the Risk Factors (WARIFA) mobile health app was created for general health awareness and to support users in adopting healthier behaviors, as well as to support type 1 diabetes (T1D) self-management.

**Objective:**

This study aims to evaluate the effectiveness of the WARIFA app with personalized artificial intelligence (AI)–driven messages, compared to a nonpersonalized version, in promoting health-related behavior change among the general population and individuals with T1D.

**Methods:**

A total of 108 European participants, including individuals with T1D, were to be randomized (computer-generated sequence, double-blind, 1:1 ratio) to an intervention or control group. In the intervention group, participants used the WARIFA app with personalized messages and the use of AI. This applied to certain functionalities, such as providing recommendations on healthy dietary habits based on food logging and offering advice and encouragement through daily step tracking. It also provided risk predictions for cardiovascular and respiratory diseases, cancer, and type 2 diabetes. Participants with T1D were offered glucose predictions based on previous measurements. In the control group, participants used a WARIFA app without personalized messages or AI. Both WARIFA app versions offered access to air quality and UV index information for the geographical area, as well as displaying physical activity in the form of daily steps and sleep hours, as well as glucose results for participants with T1D. Both groups were provided with an activity monitor and used the WARIFA app for 8-12 weeks. The primary outcome is a self-defined goal, chosen from a set of proposed objectives at baseline and assessed at the end of the study using a Likert scale (1 to 10 points, 0 being no achievement at all and 10 being full achievement of the objective). Secondary outcomes include: engagement with the app, changes in lifestyle behavior, body composition, lipid profile, glycated hemoglobin (T1D only), hypoglycemic events (T1D only), and health-related quality of life, as well as acquired knowledge, self-efficacy, and usability.

**Results:**

The clinical trial took place between January and June 2025. A total of 88 participants were finally recruited. The data are being analyzed, and the results are expected to be published in 2026.

**Conclusions:**

There is evidence that improving lifestyle behavior can prevent noncommunicable diseases. In this study, we aim to evaluate the effectiveness of the WARIFA app to improve lifestyle behaviors and T1D management.

**Trial Registration:**

ClinicalTrials.gov NCT06918444; https://clinicaltrials.gov/study/NCT06918444

**International Registered Report Identifier (IRRID):**

DERR1-10.2196/84510

## Introduction

### Background

Chronic noncommunicable diseases (NCDs) are a major global health problem. They are the leading cause of mortality and morbidity, accounting for 74% of all deaths worldwide [1]. Their management and treatment are a major economic concern, accounting for 25% of the total health care budget in Europe [2]. The major NCDs are cardiovascular diseases (CVDs), respiratory diseases, cancer, and type 2 diabetes (T2D).

CVD is the leading cause of death worldwide and in Europe, accounting for 32.7% of all deaths in 2022 [3]. Ischemic heart disease and cerebrovascular disease are the most common causes, accounting for 32.4% and 20.8% of CVD deaths, respectively [3]. There is variability between high-income and middle-income countries in the proportion of premature CVD deaths, with the proportion being higher in middle-income countries in both sexes (36% in women and men in middle-income countries, vs 16% and 24% in women and men in high-income countries, respectively) [4]. In 2019, these diseases were responsible for an estimated 70 million disability-adjusted life years in European Society of Cardiology member countries [4]. There is also an unequal distribution of CVD deaths in Europe, with more than half of all deaths occurring in eastern countries, compared with 23% in northern and western countries [1,4,5]. Metabolic risk factors include hypertension, hyperglycemia, hyperlipidemia, and obesity. Lifestyle risk factors include tobacco and alcohol use, physical inactivity, and an unhealthy diet.

Respiratory diseases are the third leading cause of death in Europe, accounting for 7% of all causes of death in 2022 [3]. Chronic obstructive pulmonary disease (COPD) and asthma are the most common respiratory diseases. COPD reduces quality of life and increases morbidity, hospital admissions, and premature death. Most COPD is preventable, and the main risk factors are smoking and air pollution [3,6].

Despite a 11.9% decrease in the standardized mortality rates between 2012 and 2022, cancer is still the second most frequent cause of death in the European Union (EU), accounting for 22.3% of all deaths in 2022. Lung, colorectal, and breast cancer account for 19.8%, 11.5%, and 7.4% of all deaths from cancer in the EU [3]. Globally, the most commonly diagnosed group of cancers is skin cancer, and cutaneous melanoma, the deadliest, accounts for 20% of skin cancers [7]. As with CVD, many cancers can be prevented by adopting a healthy lifestyle. Smoking, alcohol, physical inactivity, and an unhealthy diet, the latter 2 leading to overweight and obesity, are responsible for the majority of cancer incidence [4]. In addition, UV radiation exposure is the leading environmental cause of melanoma, a type of cancer that continues to increase in fair-skinned populations worldwide [7].

T2D has a prevalence of 5%-20% in the adult population. It is associated with other NCDs and includes risk factors such as smoking, physical inactivity, unhealthy diet, and obesity. Prevention can reduce the risk of diabetes by up to 78% and reduce cardiovascular mortality, cancer mortality, and the incidence of CVD in people with T2D [8,9].

For type 1 diabetes (T1D), there are no established recommendations for prevention. However, controlling risk factors such as smoking, alcohol consumption, sedentary lifestyle, and unhealthy diet improves disease control and delays the onset of complications such as CVD [10-13]. Therefore, while modifying these lifestyle factors does not prevent the onset of T1D, it does reduce the risk of NCDs in this specific population. It improves glycemic control and prevents other microvascular complications that are more prevalent in people with T1D, such as diabetic retinopathy [14-16]. Treatment of T1D requires a high degree of self-care, which can represent a burden and affect health-related quality of life [17]. The incorporation of technology such as continuous glucose monitoring (CGM) and automated insulin delivery systems facilitates diabetes management by providing relevant information and improved glycemic control [18,19].

The risk of developing some NCDs can be assessed based on known risk factors. This is important as we can act on those risk factors that are modifiable, provide personalized recommendations for each individual, and prevent or postpone the onset of NCDs, reducing morbidity and mortality and economic expenditure. Furthermore, the 4 major NCDs share common risk factors: physical inactivity, an unhealthy diet, and alcohol and tobacco consumption. Addressing these 4 risk factors could reduce the risk of NCDs.

An increasing number of people use mobile apps to improve their health. These apps offer direct access to information on specific health topics, as well as useful features, such as medication reminders, physical activity, and vital sign recording [20]. Artificial intelligence (AI) is also becoming an increasingly popular tool. Some studies have examined the potential application of AI in mobile health apps, particularly in relation to mental and oral health [21].

Watching the Risk Factors (WARIFA) [22] is a project funded by the European Commission and coordinated by the Norwegian Centre for E-Health Research. It involves 12 partners from 6 European countries. It aims to provide early risk assessment to enable individualized risk prevention. A mobile health (mHealth) app (the WARIFA app) has been developed, which uses user-generated data analysis and AI to provide NCD risk estimation, as well as personalized messages, based on scientific evidence, to promote healthy behaviors.

Personalized recommendations in health apps are highly relevant as they allow feedback to be tailored to each user’s actual needs in terms of content, intensity, and timing. This can lead to greater engagement, self-efficacy, and adherence to recommended behaviors. Unlike static or nonpersonalized recommendations, just-in-time, adaptive interventions provide the right recommendations at the right time, taking the context of each user into account. This type of intervention is commonly used in health apps [23-26]. Thus, personalized interventions provide more than just general information; they also seek to maximize the timeliness and relevance of each recommendation by finding the most appropriate moment to encourage adherence. The WARIFA app takes this approach by integrating automatically received data (from activity devices) and user-entered data to continuously adapt its recommendations. For example, it adjusts physical activity suggestions according to daily steps and generates dietary recommendations according to daily consumption records.

Co-creation methodology was used during the development of the WARIFA app. This involved the users throughout the process, enabling their needs to be identified and feedback to be obtained. Eighteen focus groups consisting of 3-10 participants of different ages from the general population and people with T1D were organized for this purpose. The co-creation process was divided into 2 phases.

In the first phase, focus groups were held with participants who expressed their needs and expectations for a health app and created hand-drawn sketches and prototypes. In the second phase, focus groups were held with a prototype of the app based on users’ preferences from the previous phase. Quantitative and qualitative information obtained from each group was used to update the app, creating one that aligns with the real needs of the population.

After the co-creation process, the randomized controlled trial (RCT) whose protocol is described in this article was conducted to evaluate the effectiveness of the WARIFA app in promoting healthy lifestyles and in the self-management of T1D.

### Objective and Hypothesis

The aim of this RCT is to evaluate the effectiveness of the WARIFA app in promoting healthy lifestyles and in the self-management of T1D.

The hypothesis is that use of the WARIFA app will improve healthy eating habits, increase physical activity, reduce alcohol consumption, promote smoking cessation, and improve sun protection behaviors. In addition, it is expected to reduce hypoglycemic events and lower glycosylated hemoglobin A_1c_ (HbA_1c_) in people with T1D.

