My day: a diary is available to record various items [Figure 1H]. Participants are able to easily and intuitively record their fruit and vegetable intake, alcohol and tobacco consumption, and sunscreen use every day. They are able to customize the diary to choose the items they want to record. They see a graphical presentation of the records of the last 7 days, with a marker for their personal goal [Figure 1I], as well as individual and personalized messages generated with the use of AI for the improvement of their goals. People with T1D can also record their hypoglycemic events.Assess your lifestyle: participants complete questionnaires that provide data for WARIFA to personalize their risk estimation and recommendations. These questionnaires include basic variables (age, gender, weight, and height), lifestyle habits (alcohol consumption, smoking, and physical activity), eating habits, and sun exposure, as well as additional risk factors for melanoma. Once the questionnaires have been completed, the app delivers the first messages with personalized recommendations. If the user enters this section at another stage in the trial and changes data in the questionnaires, new recommendations are generated and delivered to the user.My top recommendations: personalized recommendations appear for each participant each day, based on the data obtained through the initial questionnaires and how far they are from the recommended target for each item (Figure 1A). These recommendations are based on scientific evidence and updated World Health Organization guidelines.My health predictions: will give access to risk calculators (Figure 1B) for different NCDs (T2D, CVD, COPD, and melanoma) with personalized risk estimation over the next 10 years. During the WARIFA project, some risk calculators were developed, including the cardiovascular risk calculator for T1D [29]. The melanoma risk calculator was developed based on the first primary risk prediction tool created by the Melanoma Institute Australia [31]. The FINDRISK calculator, which has been validated in several European countries, is used to calculate the risk of T2D [32]. To calculate cardiovascular risk in the general population, the SCORE2/SCORE2OP calculator was used; this has been validated in the European countries participating in the study [33,34]. Finally, the self-scored COPD population screener questionnaire [35] was used to screen for COPD in smokers, since there is no COPD risk calculator validated in the European population. In all cases, the personalized risk of the different NCDs is accompanied by an explanatory message. If the COPD-Q score is high, it is recommended that participants visit their health service physician for further assessment.My community: through the use of geolocation (if permission is granted), it provides personalized recommendations based on the UV and air quality indices in the participant’s geographical area (Figures 1C,1D,1E,1F, and 1G). A link to a web page [36] with additional health-relevant information (air pollution and UV rays, statistics on NCDs of the population, lifestyle habits...) about the area where the user is located is also displayed.Step functionality: shows the number of steps taken by participants at any point in each day, as well as a graphical presentation of the number of steps for the last 7 days (Figure 1J). Recording is automatic via the physical activity monitor.Heart rate function: shows the current heart rate and a graph with its evolution in relation to the measurements in the last 24 hours. The source of the data is the physical activity monitor.Sleep function: shows today’s hours of sleep and a bar graph of the hours of sleep the last 7 days recorded by the physical activity monitor.Diabetes functionality: people with T1D can view their glucose data in near real time (with a delay of 30 minutes) by connecting to the glucose sensor (Figure 2). They can also view historical glucose data through various graphs, such as time in different ranges (Figures 2B and 2C), glucose management index, and hypoglycemic events. Using AI, they receive an estimate of the interstitial glucose prediction over the coming 30 minutes and 2 hours (Figure 2D), as well as a personalized risk of nocturnal hypoglycemia (Figure 2A).Settings and other functions: in this section, participants can customize which parts of the WARIFA app they want to see, as well as the notifications, sounds, fonts, and language used.

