### Outcomes

#### Overview

The primary outcome is a participant-defined goal, whose fulfillment is assessed at the end of the study using a Likert scale ranging from 1 (“far below expectations”) to 10 (“far above expectations”) [38].

Participants can choose their own goal from a range of options: increase fruit and vegetable consumption, increase physical activity, reduce alcohol consumption, stop smoking, improve sun protection behavior, and reduce the number of weekly hypoglycemic episodes (the latter only for T1D participants).

The secondary outcomes are: frequency of app use, time spent using the app, consistency in data recording, changes in eating habits, increase in physical activity, reduction in smoking and alcohol consumption, changes in sun protection behavior, total cholesterol, high-density lipoprotein (HDL) cholesterol, low-density lipoprotein cholesterol, non-HDL cholesterol, triglycerides, weight, BMI, body fat, lean mass, abdominal, waist and biceps circumference, abdominal skinfold thickness, tricipital skinfold thickness, dynamometry, sit to stand 5 repetitions test, perceived quality of life, acquired knowledge, self-efficacy, and usability.

For participants with T1D, hypoglycemic events (number of episodes of at least 15-minute duration with a glucose concentration of <70 mg/dL according to the CGM and manually registered episodes), HbA_1c_, average glucose (average glucose in mg/dL over the last 14 days), glucose management indicator (a measure of glycemic control calculated from average glucose, which is an estimation of HbA_1c_) and time in target range (% of time in the last 14 days that glucose is within (70-180mg/dL), below (<70 mg/dL), above (181-240 mg/dL), or significantly above (>240 mg/dL) the recommended target will be measured.

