#### Behavior Change

Changes in dietary habits, tobacco and alcohol consumption, and sunscreen use are measured by diary entries. Changes in physical activity (steps) are automatically measured by the physical activity monitor.

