### Statistical Analysis

Descriptive results will be presented as mean (SDs), or median (IQRs) for continuous variables, and frequencies and percentages for categorical variables. The primary endpoint is the difference in Likert score between the 2 groups in the self-reported achievement of the individual, self-defined aim at the end of the study. The intervention and control groups will be compared using a Student *t* test (2-tailed) or a Mann-Whitney *U* test. We will also perform linear regression to compare the groups with adjustment for the stratification factor center. For comparison of changes in variables measured at baseline and end of study, we will use linear regression or logistic regression adjusting for the baseline measurement [48]. Logarithmic transformation may be used. A *P* value below .05 will be considered significant.

An intention-to-treat analysis will be performed (including all randomized participants, regardless of their adherence to the intervention).

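### The hypothesis is about smoking cessation, but the only smoking outcome for all participants is a reduction in consumption; the diet measure is narrower than its label, and both rest on a diary that controls lack

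*Protocol article*

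**What the plan says.** The protocol article's Objective and Hypothesis section expects that the app "will improve healthy eating habits, increase physical activity, reduce alcohol consumption, promote smoking cessation" and will improve sun protection. Alcohol is to be reduced, whereas smoking is to be given up.

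Under Outcomes, Overview, the goals a participant may choose for the primary outcome include "increase fruit and vegetable consumption, increase physical activity, reduce alcohol consumption, stop smoking". The secondary outcomes include "changes in eating habits, increase in physical activity, reduction in smoking and alcohol consumption, changes in sun protection behavior". Here smoking and alcohol share one term, reduction.

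The Behavior Change section names the instrument: "Changes in dietary habits, tobacco and alcohol consumption, and sunscreen use are measured by diary entries". The Intervention section describes the diary as the place where participants "record their fruit and vegetable intake, alcohol and tobacco consumption, and sunscreen use every day", and lets them choose which items to keep. The Control Group section lists the diary among the functions that the control version does not have.

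The Statistical Analysis section defines the primary endpoint as the "difference in Likert score between the 2 groups in the self-reported achievement of the individual, self-defined aim".

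**The concern.** Stopping smoking and smoking less are different quantities, and an intervention can change one without the other. With only the amount smoked as an outcome, the trial could report a favourable smoking result that says nothing about the cessation it set out to promote.

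Diet has a milder form of the same problem. The label in the outcome list fits the hypothesis, but the named instrument appears to capture one component of diet.

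The instrument also raises a problem for both outcomes. If change is read from a diary that one arm does not have, there is no between-arm comparison for the hypothesis to rest on.

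**Working it through.** The article gives no figure for smoking or diet to reproduce; its sample size concerns the Likert score only. The check is therefore a comparison of passages, followed by an illustration of size.

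**Smoking, side by side**

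- Hypothesis: cessation.
- Selectable goal: stopping.
- Secondary outcome: "reduction in smoking and alcohol consumption".
- Instrument: diary entries of tobacco consumption.

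Three other places might supply a cessation measure:

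1. *Primary outcome.* Each participant rates achievement of one chosen goal, and the scores are pooled over all goals. The pooled score cannot isolate cessation, and it covers smoking only for those who chose that goal.
2. *Diabetes self-care questionnaire* (Knowledge and Attitudes). It has a yes/no smoking item, but it is an instrument for people with diabetes, so it does not serve the general population.
3. *In-app lifestyle questionnaire* (Intervention). It asks about smoking, but it is described as input for personalization, and Behavior Change names the diary as the measure.

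**Diet, side by side**

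- Hypothesis: healthy eating habits.
- Outcome label: changes in eating habits. These agree.
- Instrument: the diary, whose only named food item is fruit and vegetable intake.

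The gap is therefore between the label and the instrument. The Abstract mentions food logging and the Background mentions records of daily consumption, so wider dietary data may exist, but no further diary item is named.

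**Control arm**

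Behavior Change relies on the diary and Control Group removes it. Control Group also says that data collection is similar in the two arms, but it does not say what replaces the diary for tobacco and food.

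**Illustration of size**

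The cigarette counts, smoking prevalence and quit counts below are assumptions; none is in the article.

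- Every intervention smoker falls from 15 to 7.5 cigarettes a day and nobody quits in either arm. Reduction in amount = (15 - 7.5)/15 = 50%. Difference in the proportion who quit = 0.
- Number of smokers: 88 × 0.10 = 8.8 and 88 × 0.30 = 26.4, so about 9 to 26 in total, or 4 to 13 per arm.
- Two-sided Fisher exact test with equal arms of size m and k quitters versus 0: P = 2 × C(m,k)/C(2m,k).
  - m = 9, k = 3: 2 × 84/816 = .206.
  - m = 9, k = 4: 2 × 126/3060 = .082.
  - m = 9, k = 5: 2 × 126/8568 = .029.
  - m = 13, k = 4: 2 × 715/14950 = .096.
  - m = 13, k = 5: 2 × 1287/65780 = .039.

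With 9 or 13 smokers per arm, five quitters against none would be needed to fall below .05.

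**The case against.** The strongest reply is that these are secondary outcomes in a condensed article. One primary endpoint is defined, and no success criterion is set on any secondary outcome. The Discussion restates the hypothesis in terms of self-defined objectives and behavior change, and concedes that the sample may be too small for many secondary outcomes. The hypothesis speaks of promoting cessation and does not name a quit rate. Coding of outcomes is commonly left to the full protocol or analysis plan. Table 1 schedules questionnaires at the initial and final visits, and logistic regression is foreseen, so a binary smoking outcome may be intended.

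Much of this stands as a limit on the point. A reader might infer that a positive result would support neither the smoking nor the eating claim, or that the stated diet outcome is merely a fruit and vegetable record. The documents do not support either reading. The diet outcome as listed matches the hypothesis, fruit and vegetable intake is a component of healthy eating, and a gain in it would be partial support. Wider food records are also hinted at.

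The reply does not remove the smoking mismatch. The article itself states the hypothesis, the outcome and the instrument, and they disagree. A cessation outcome held only in an unseen document would leave the published outcome list incomplete. Nor does the reply explain how diary outcomes are compared with an arm that has no diary.

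**Conclusion.** The point holds firmly for smoking and in a limited form for diet. As written, the plan would not test cessation: a reduction in amount with no quitters would look like a benefit. For diet, a rise in diary fruit and vegetable intake would be partial evidence and would not by itself establish healthier eating overall. Both outcomes also depend on an instrument absent from the control app.

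The practical size is modest. If 10-30% of participants smoke, a correctly defined cessation outcome would involve about 4 to 13 smokers per arm and would be imprecise whatever the analysis. The gain lies in having the reported claim match what was measured. It should be settled before results are reported; the article says the data are still being analyzed.

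**What to change.** **Smoking.** Add an outcome: not smoking at end of study (yes/no) among those who smoked at baseline, taken from the in-app lifestyle questionnaire at the initial and final assessments. First confirm that this questionnaire is among those in Table 1, which does not name them; the Intervention section describes later changes to it only for users who return to that section. Report quitters per arm with an exact or Firth-penalised comparison, and label the result imprecise. The baseline-adjusted logistic model in Statistical Analysis does not suit this outcome: baseline status is constant among smokers, and an arm with no quitters gives ordinary logistic regression no finite estimate. Keep the amount smoked as supportive.

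**Diet.** Use the eating-habits questionnaire at baseline and end as the between-arm measure, subject to the same confirmation, or limit the claim to fruit and vegetable intake.

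**Instrument.** Reconcile Behavior Change with Control Group by stating where control-arm tobacco and food data come from. Restating the hypothesis as lower tobacco consumption or higher fruit and vegetable intake is not enough alone, because a diary measure would still be missing in controls. If no final questionnaire data exist, say so and make no cessation claim.

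**Cost.** Wording changes and one small analysis, if the data were collected. The cessation estimate will be imprecise and the claims narrower.
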